### Trial design

2.3.

This study design involves a two-arm cluster-randomized-controlled trial conducted with adolescent males ages 13–19 recruited from youthserving community agencies in Pittsburgh, PA. Twenty-one clusters from 20 neighborhoods were randomly allocated to the intervention or control arm. Participants (n = 866) complete surveys prior to program implementation (baseline) and immediately following the program (end of program, EOP). Follow-up surveys are collected 3 months (T2) and 9 months (T3) after end of program. Baseline surveys are completed in-person using tablets to complete the survey online; EOP, T2, and T3 are also completed in-person on a tablet or remotely using survey links that are texted or emailed to participants using contact information provided with recruitment. Retention is facilitated by collecting detailed contact information and offering incentives for survey completion ($50 total for baseline, feedback surveys throughout the program, and EOP; $30 for T2; $50 for T3) (see Fig. 2 for study flow).

### Participants, interventions, and outcomes

2.4.

#### Study setting and site eligibility criteria

2.4.1.

This study involves 20 neighborhoods and 21 clusters in the Pittsburgh area; within each neighborhood, one to four different community partner organizations (referred to as “community partners” here) participated. Neighborhoods were recruited by identifying a potential community partner who could host the program and were willing to be randomized to receive the intervention or control programming. These community partners included youth-serving organizations, YMCA, Urban League, faith-based organizations, and libraries. Additionally, we partnered with the county’s community intensive surveillance program, a diversion program for youth involved in the juvenile justice system.

Neighborhoods were identified based on having sites where the YMCA, Urban League, or other youth serving partners had existing programs and which were considered lower income communities based on census information and school district data. Asset maps were created for each neighborhood with the goal of identifying community champions and youth-relevant resources to support this community-based project. The strong partnerships established with key stakeholders in each of these sites (including site coordinators, facilitators, and community members) facilitated recruitment and retention as described below.

Among the 20 participating neighborhoods, the proportion of students attending public high schools in those neighborhoods considered economically disadvantaged ranges from 32 to 100%; the high school graduation rate for those same school districts ranged from 63 to 97%. Each of these neighborhoods struggle with poverty, school ‘push-out’ (disciplinary actions that push youth, especially African American boys, out of the regular school system), and among the highest rates of gang and gun violence in the county (see Table 1 for neighborhood characteristics). These characteristics were compared by treatment arm using Kolmogorov-Smirnov two-sample exact tests due to their nonnormal distributions. Neighborhood characteristics did not vary between the intervention and control arm neighborhoods.

Within the 20 participating neighborhoods, there were a total of 40 sites/community partners/locations approached and 38 agreed to participate. The composition of the participating sites included 11 places of worship, 20 community centers, 2 public libraries, and 5 juvenile justice community intensive surveillance program centers. One site (cluster) was located at the downtown Urban League office and consisted of youth involved in an African American young men’s leadership group who came from several different neighborhoods and schools in the Pittsburgh area.

#### Participant eligibility criteria

2.4.2.

Manhood 2.0 was designed for high school age youth for implementation in community-based settings. Eligible youth were between the ages of 13 to 19, who identified themselves as male, were residents in the neighborhood where the site was located, and were willing to participate in an 18 h gender-specific program. Youth were allowed to participate in the program (intervention or control) without participating in the research.

### Experimental and control arms

2.5.

Program Delivery: Both experimental and control arm interventions involved 18 h of curriculum, generally spread out over 3 to 6 week periods. The program was delivered with some variation in schedules to meet the needs of community partners and participating youth. Such configurations included but were not limited to: three 6-h sessions spanning three weekdays during the summer (for job skills training only), nine 2-h sessions held twice per week on weekday evenings, and six 3-h sessions held once or twice per week on weekday evenings or Saturday afternoons (which was the preferred and most commonly used design).

Fidelity to intervention: For both intervention and control arms, research assistants were present at every session to track attendance, facilitate program implementation logistics (such as ordering food), and to complete detailed fidelity forms that assessed facilitators’ ability to deliver the content of the program as intended.

### Manhood 2.0 (experimental arm)

2.6.

In prior implementations of the Program H curriculum in international settings, we found that intensive sessions spread over a period of several weeks results in greater uptake by youth and is more feasible in community settings (rather than trying to schedule a 3 day consecutive, overnight event that incurs significantly more resources) [29,54].

Program Content: Manhood 2.0 guides youth to explore and reflect upon social constructions of masculinity, describe healthy relationships, discuss healthy sexual behaviors, identify coercive and disrespectful behaviors, and practice skills to intervene when witnessing peers’ disrespectful and harmful behaviors, with repeated reflection on gender norms throughout these sessions. The curriculum involved three main topic areas. The first focuses on the theme of gender, masculinity and power, allowing the young men to actively reflect on the messages and expectations that they have received from society about manhood and gender norms. The second topic focuses on the theme of violence. This includes several components: an exploration of the various forms of violence, its impact on communities, and the role that masculinity may contribute; identifying healthy versus unhealthy romantic relationships; sexual consent and decision making; and bystander interventions when witnessing abusive behavior. The final topic area focuses on sexual and reproductive health, which includes providing information about sexual health and contraception, condom and contraceptive demonstrations, tying health behaviors and access to health facilities to conceptions of masculinity, and opportunities to ask medical professionals sexual health-related questions.

### Job skills curriculum (control arm)

2.7.

The job skills readiness program was developed and tested, and is widely used throughout the county, called “Jump Start Success Work Readiness and Career Exploration Training” (http://www.youthworksinc.org/jumpstart_success/index.html). The sessions were set up to mimic the timing for the intervention curriculum (18 h curriculum).

Program Content: The curriculum covers topics from career options and goal setting to interviewing skills. The entire curriculum involves 9 modules. For the purposes of this study, the facilitators focused on the first 6 modules (to mimic Manhood 2.0 structure) with an emphasis on goal setting, future orientation, learning about building a resume, interviewing skills, and workplace expectations.

### Training of facilitators for control and intervention

2.8.

The initial training for Manhood 2.0 occurred over 3 days to develop a core group of facilitators for the study. The first 2 days involved understanding the program’s methodology, learning more about the activities and the opportunity to practice activities for feedback from their colleagues; the final day involved a pilot with boys from a school district not involved in the study who provided feedback on the curriculum for further refinement. Because *Jump Start* is an established program with an experienced facilitator, an initial training for the facilitator of the control group was not necessary.

Subsequent trainings for both the control and experimental programs were primarily comprised of one on one and/or small group mentorships, using an apprenticeship model, where the facilitator(s) shadowed and worked alongside an experienced lead facilitator at a site, for the entire 18-h curriculum. This model enabled facilitators to pair with a lead facilitator and work their way from observing a discussion and/or session to co-facilitating to finally leading a complete session on their own, through an iterative process encompassing a series of check-ins, evaluations, and feedback. During the observation process, facilitators were encouraged to experience and examine all elements of the program, particularly activity and session flow and timing and the dynamic between facilitators and participants and amongst participants themselves. In addition, during the observation period, facilitators were required to review and become familiar with the curriculum. Depending on experience and comfort level, facilitators were welcomed to engage in discussion. Facilitators were deemed ready to lead a session if they had participated as a co-facilitator, were observed leading each activity, and if the feedback forms from youth and fidelity checks conducted by research assistants consistently showed adherence to program content. This approach to training community-based facilitators creates a longer-term sustainability plan, with lead facilitators training newly interested facilitators from their community.

After each session, the facilitator would reconvene with the lead facilitator to debrief and examine implementation. Participant engagement and behavior, program delivery and timing, and learning objectives were priority topics addressed during debriefing. These elements were also captured on fidelity forms completed by research assistants during each program session. Post-session development also included biweekly check-ins with project coordinators to analyze feedback and fidelity forms. These meetings ensured maintenance of fidelity and program goals, in a timely fashion. If facilitators needed to improve on the delivery of a certain activity or topic or if there were issues with engagement, immediate action was taken to directly address the situation and work towards better implementation for the subsequent session.

Separate conferences (generally every two to three months) were held for job skills intervention facilitators to support facilitators in their development. All facilitators were required to attend these conferences to share their perspectives on the program and also receive collective feedback on overall implementation. Conferences allowed for teambuilding and training. Lastly, extra source materials such as videos, websites, articles, and other media were consistently provided or recommended to support development of facilitator knowledge and skills and keep content up to date.

### Outcomes

2.9.

All outcomes are collected via self-report on anonymous surveys by participants (Table 2).

### Primary outcome

2.10.

#### SV/ARA perpetration

2.10.1.

At baseline and T3 (9 months post-intervention), participants report whether they perpetrated the following SV or ARA behaviors in the last 9 months. The primary outcome measure for the study is any report of SV or ARA perpetration, i.e., yes to any of the following items.

The following two constructs focus on ARA behaviors against a dating partner. “Any ARA perpetration” is measured as a yes to any of these 13 items.

#### Physical/sexual relationship violence

2.10.2.

Three items are used to assess physical or sexual violence perpetration against a partner or ex-partner [79]. Participants report whether they performed each action, which is dichotomized as yes to any. Examples include “hit, pushed, slapped, choked or otherwise physically hurt someone you were going out with or hooking up with?” and “used physical force or threats to make someone you were going out with or hooking up with have sex (vaginal, oral, or anal sex) when they didn’t want to?”

#### Dating abuse

2.10.3.

A ten-item scale, developed for use with high school-aged students, is used to assess whether the participant perpetrated any abuse against a dating partner [37]. Examples include “convinced them to have sex, after they said no a few times” and “told them not to talk to others or told them who they could hang out with. ” A positive response to any of these items is counted as any ARA perpetration.

“Any SV perpetration” is measured as yes to any of the sexual relationship violence and dating abuse items above as well as yes to any of the behaviors below.

#### Non-partner sexual violence

2.10.4.

To measure whether a participant committed sexual violence against a *non-partner,* the two sexual IPV items were modified to query for people they had NOT gone out with or hooked up with, and included friends, family, and strangers [79]. Responses are dichotomized as yes to any.

#### Incapacitated sex

2.10.5.

Participants are asked if they had done something sexual with someone when that person was “too drunk or high to stop you,” [80] with a response of “yes” coded as yes to incapacitated sex.

#### Use of drugs or alcohol on purpose for sex

2.10.6.

Participants are asked whether they had purposely given someone alcohol or drugs to do something sexual with that person [81]. A response of “yes” is coded as yes to use of drugs or alcohol on purpose for sex.

#### Sexual harassment

2.10.7.

Five items assess the frequency with which a participant has engaged in sexual harassment against someone from “making unwanted sexual comments” to “touching or grabbing them in a sexual way.” [82,83] Any endorsement of these behaviors is coded as yes for sexual harassment.

#### Cyber sexual abuse

2.10.8.

Given the ubiquity of social media and smartphones, three items assess for frequency of sexual harassment, including “try to get them to talk about sex when they did not want to” and “post or publicly share a nude or semi-nude picture of them” using mobile apps, social networks, texts, or other digital communication [3,84,85]. Any endorsement is coded as yes for cyber sexual abuse.

### Secondary outcomes

2.11.

#### Positive bystander intervention behaviors

2.11.1.

A scale developed for use with high school students is used to determine whether participants will intervene or interrupt in a positive manner when they witness disrespectful or abusive behaviors by peers [37]. The scale first assesses whether participants had witnessed nine different abusive behaviors among their peers (e.g., “making rude or disrespectful comments about a girl’s body, clothing, or make-up”). For each behavior witnessed, participants are asked if they performed three positive behaviors (e.g., “I talked to an important adult about it”). Reporting at least one positive response per behavior witnessed is summed for the 9 items, creating a maximum summary score equal to 9.

#### Condom negotiation self-efficacy

2.11.2.

A 5-item scale is used to assess how confident participants feel about negotiating condom use with a partner [86]. Three positive (e.g., “I feel confident in my ability to suggest using condoms with a new partner”) and two negative (e.g., “If I were unsure of my partner’s feelings about using condoms, I would not ask my partner to use one”; reverse coded) are used. Responses are on a 5-point Likert scale, with values from “strongly disagree” to “strongly agree.” The scale is analyzed using the mean score.

#### Attitudes related to condom and contraceptive use

2.11.3.

A 10-item scale evaluating the participants’ temperament towards the usage of condoms and other contraceptive modalities. Examples of these 10 items include [87–90], “using birth control makes sex feel unnatural” and “I am in favor of my partner and me using birth control. The attitudes are measured by utilizing a 5-point Likert scale from “strongly disagree” to “strongly agree” and a mean score is calculated; a higher score indicates a more positive attitude towards condom and contraceptive use.

#### Recognition of ARA

2.11.4.

Recognition of abusive behaviors is measured with a 12-item scale that addresses the ability of participants to recognize offensive and harmful actions against a partner as abusive [91]; for example, “name calling or insulting them” and “threatening to hit them”. Responses range on a 5-point Likert scale from “strongly disagree” to “strongly agree. ” A mean score across the 12 items is calculated, with the higher score indicating higher recognition of abusive behaviors.

#### Gender equitable attitudes

2.11.5.

A 13-item scale is utilized to measure participants’ views on gender-equitable norms [37,92,93], such as, “A guy never needs to hit another guy to get respect” and “I would be friends with a guy who is gay”. Response options are on a 5-point Likert scale from “strongly disagree” to “strongly agree” and a mean score across the 13 items is calculated. A higher mean is indicative of more equitable attitudes.

#### Intentions to intervene with peers

2.11.6.

Utilizing eight items, this attitudinal measure assesses the likelihood for a participant to intervene when witnessing a range of harmful behaviors amongst male peer students, similar to the scenarios for assessing actual bystander intervention behaviors described above [37]. Responses are on a 5-point Likert scale from “very unlikely” to “very likely” and a mean score across the eight items is calculated; a higher score indicates greater intentions to intervene.

### Sample size

2.12.

Power and sample size calculations were based on clinically meaningful differences between treatment groups with respect to changes in the outcomes across time (i.e. intervention effect). For the primary outcome - any SV/ARA perpetration at Time 3, the detectable difference between arms was calculated based on traditional methods that assumed a fixed number of clusters as well as fixed number of subjects per cluster [94]. Twenty-one clusters were randomized, assuming a within-cluster intra-class correlation (ICC) of 0.01 (within-school correlations for abuse perpetration, similar to our team’s prior work with a related sexual violence prevention program with male athletes [37,95]), and a 20% baseline SV perpetration rate in the control arm. With 866 participants (approximately 41 boys at each site) and an 80% retention rate at Time 3, we expect to have 80% power to detect an absolute difference in SV perpetration of 8.3 (42% relative decrease) due to the intervention. We anticipate having ample power to detect clinically meaningful changes in bystander behaviors and the secondary outcomes as well. Based on previous studies, the within-cluster ICCs for each of our secondary outcomes ranged from 0.006 to 0.01. If we assume the upper end of that range, we will have at least 80% power to detect standardized mean differences as small as 0.23 between study arms.

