#### Randomization

2.16.1.

Randomization was performed at the neighborhood level (i.e., cluster) to reduce risk for contamination. The initial randomization included 10 clusters that were assigned to experimental or control conditions. The study statistician performed this randomization, stratifying by lead site in that neighborhood (YMCA, Urban League, or Other), such that within each stratum, each site/neighborhood had a 50/50 chance of being assigned to intervention or control. Due to a combination of lower-than-expected recruitment by neighborhood (target = 96 participants each) and the interest from other community partners, we individually randomized an additional 11 neighborhoods, stratified by type of site. This resulted in a total of 21 clusters randomized, with 11 assigned to experimental and 10 assigned to control. All neighborhoods in the study met the original criteria of being socially or economically disadvantaged and/or predominantly African American.

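### The detectable differences in section 2.12 assume equal cluster sizes that the recruitment makes implausible, so they are somewhat too favourable; the effect is modest and adds to a larger retention discrepancy

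*Protocol article*

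**What the plan says.** The sample size section (2.12) describes the method for the primary outcome as "traditional methods that assumed a fixed number of clusters as well as fixed number of subjects per cluster". Its inputs are: "Twenty-one clusters were randomized, assuming a within-cluster intra-class correlation (ICC) of 0.01"; "a 20% baseline SV perpetration rate in the control arm"; and "With 866 participants (approximately 41 boys at each site) and an 80% retention rate at Time 3". The result is that "we expect to have 80% power to detect an absolute difference in SV perpetration of 8.3 (42% relative decrease"). For the secondary outcomes, taking the upper end of an ICC range of 0.006 to 0.01, it claims at least 80% power for 0.23 SD. No allowance for variable cluster size is mentioned.

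Other sections describe how the clusters filled. Section 2.4.1 says that "within each neighborhood, one to four different community partner organizations" took part, and that "there were a total of 40 sites/community partners/locations approached and 38 agreed to participate". The sites range from places of worship and libraries to juvenile justice centers, and one cluster is a single downtown leadership group. Section 2.13 says recruitment ran until the overall sample size was reached and mentions no quota per cluster. Section 2.16.1 reports that 11 neighborhoods were added to the first 10: "Due to a combination of lower-than-expected recruitment by neighborhood (target = 96 participants each"). The Results give 464 youth in 11 intervention clusters and 402 in 10 control clusters.

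**The concern.** At a fixed total and a fixed ICC above zero, any spread in cluster size lowers the effective sample size. The calculation sets that spread to zero. Exact equality is impossible, since 464/11 = 42.2 and 402/10 = 40.2 are not whole numbers, and the recruitment history points to a spread well beyond rounding. The Discussion also expects missing data to be concentrated in rounds with justice-involved youth, which would make the analysed clusters more uneven still.

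At stake is how a null result is read. The 8.3-point and 0.23 SD figures are the trial's statement of what it could detect. If they are too favourable, a null result looks like stronger evidence of no effect than it is.

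**Working it through.** **Inputs.** From 2.12: 21 clusters, ICC 0.01, control rate 20%, difference 8.3 points (20% vs 11.7%), 866 youth, 80% retention (0.8 × 866 = 693). From 2.18: two-sided 5%. Assumed: the CV of cluster size, which the document does not give.

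**Formulas.** Effective N is Ne = N/DE, with n = Ne/2 per arm.
- Equal clusters: DE = 1 + (m − 1)ICC, where m = N/21.
- Unequal clusters, conventional: DE = 1 + ((1 + CV²)m − 1)ICC.
- Unequal clusters, mixed-model weighting: Ne = Σ mᵢ/(1 + (mᵢ − 1)ICC), averaged over simulated gamma-distributed sizes.
- Power for proportions: Φ{[d − 1.96√(2p̄q̄/n)] / √((p₁q₁ + p₂q₂)/n)}. Power for means: Φ(δ√(n/2) − 1.96).

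**Step 1: reproduce the stated figures.** With all 866 youth and equal clusters, m = 41.2, DE = 1.402 and Ne = 617.5. Then [0.083 − 1.96 × 0.0294]/0.0292 = 0.87, which is 81% power. The detectable differences are 8.2 points and 0.226 SD, close to the stated 8.3 and 0.23.

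With the stated 80% retention, m = 33.0, DE = 1.320 and Ne = 524.9. Then [0.083 − 1.96 × 0.0319]/0.0317 = 0.65, which is 74% power. The detectable differences are 8.85 points and 0.245 SD, and power for 0.23 SD is 75%. The stated inputs therefore miss the stated figures before cluster size is considered.

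**Step 2: a plausible CV.** Take 38 sites over 21 clusters, one to four sites each, with both extremes present (mean 1.81).
- Least spread: 6 clusters of 1, 14 of 2 and 1 of 4. The variance is 78/21 − 1.81² = 0.44, so CV = 0.37.
- Most spread: 15 of 1, 1 of 3 and 5 of 4. The variance is 104/21 − 1.81² = 1.68, so CV = 0.72.

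These are CVs of sites per cluster. They equal the CV of cluster size only if every site recruits equally. Using the 20 neighborhoods instead of 21 clusters gives 0.33 to 0.72.

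**Step 3: the effect of unequal size.** Each cell runs from mixed-model weighting to the conventional design effect.

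| CV | Power for 8.3 points, N = 866 | Detectable, N = 866 | Power for 8.3 points, N = 693 | Detectable, N = 693 | Power for 0.23 SD, N = 693 |
|---|---|---|---|---|---|
| 0 | 80.8% | 8.23 | 74.1% | 8.85 | 75.0% |
| 0.37 | 79.8–79.2% | 8.32–8.37 | 73.1–72.7% | 8.94–8.98 | 74.0–73.6% |
| 0.5 | 78.9–78.0% | 8.40–8.49 | 72.3–71.6% | 9.02–9.09 | 73.2–72.4% |
| 0.7 | 77.3–75.3% | 8.56–8.74 | 70.8–69.2% | 9.17–9.31 | 71.7–70.1% |

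At N = 866 the loss from unequal size alone is 1.0 to 1.6 power points at CV 0.37 (80.8 less 79.8 or 79.2), 1.9 to 2.8 at CV 0.5 and 3.5 to 5.5 at CV 0.7. Applying the stated retention with equal clusters costs 80.8 − 74.1 = 6.7 points.

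**The case against.** The equal-size assumption is disclosed, so this is a simplification and not an arithmetic slip. That is fair as a description, but disclosure does not make the 80% true for the clusters actually recruited.

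The CV is undocumented. The 0.37 to 0.72 range needs equal recruitment per site, and the low-recruitment remark does not say how unequal the clusters were. This stands: the direction is secure, the size is not. On the 866 basis, a CV up to about 0.25 leaves 80% power for 8.3 points, and a CV up to about 0.37 still leaves 80% for 0.23 SD.

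A reader might add everything up and say that unequal clusters put power 8 to 12 points below the claim. The document does not support that, because most of such a gap is the 80% retention. Nor does it prove that retention was left out: an ICC near 0.005 with retention also gives about 8.3 points and 0.23 SD, although 2.12 states 0.01.

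A reader might also take these figures as power for the planned analysis. They are not. Section 2.18 adjusts for the baseline value of each outcome. For the continuous outcomes, the information lost is about 5% at CV 0.5 (589/617.5) and 8% at CV 0.7 (566/617.5) under mixed-model weighting. A baseline correlation of about 0.2 to 0.3 would offset that (r² of 0.05 to 0.08). The document gives no such correlation and credits none in 2.12.

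The ICC matters more: with 866 youth in equal clusters, power is 85% at ICC 0.006 and 75% at 0.015. Finally, the planned random cluster effects accommodate unequal clusters, so the analysis model is not in question. Only the stated detectable differences are.

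**Conclusion.** The point holds in a modest form. The detectable differences in 2.12 rest on equal clusters that the recruitment account makes implausible, and they are somewhat too favourable for that reason. Unequal size alone costs about 1 to 5.5 power points for the primary outcome over CV 0.37 to 0.7 and adds 0.1 to 0.5 points to the detectable difference.

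It comes on top of the larger retention discrepancy. With both, power for 8.3 points is about 69 to 73%, the detectable difference is about 8.9 to 9.3 points, and power for 0.23 SD is about 70 to 74%. All of this assumes ICC 0.01, a 20% control rate, no credit for baseline adjustment, and a CV that the document does not report.

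**What to change.** Recompute both detectable differences in 2.12 from the actual 21 cluster counts, at the stated 80% retention. Use either Σ mᵢ/(1 + (mᵢ − 1)ICC) within each arm or the design effect 1 + ((1 + CV²)m − 1)ICC. Report the CV of cluster size, restate the primary and secondary figures, and say whether baseline adjustment is credited and, if so, with what correlation.

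The cost is one calculation and a wording change. Enrolment and the analysis model stay as they are. The drawback is that the stated figures become slightly less favourable.

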	Primary Outcome: Any Sexual Violence/Adolescent Relationship Abuse Perpetration (comparing differences between intervention and control at Time 3)					
Physical/sexual IPV [79]	Yes/no to each Modeled as yes to any lifetime (baseline only) and yes to any past 9 months	X			X	*Have YOU done any of the following to someone you were in a relationship with (like he or she was your partner/girlfriend/boyfriend, you were dating or going out with, them) or hooking up with:* 1. …[ever/in the past 9 months] hit, pushed, slapped, choked or otherwise physically hurt someone you were going out with or hooking up with? (include such things as hitting, slamming into something, or injuring with an object or weapon.) 2. …[ever/in the past 9 months] used physical force or threats to make someone you were going out with or hooking up with have sex (vaginal, oral, or anal sex) when they didn’t want to? 3. … [ever/in the past 9 months] had sex with someone you were going out with or hooking up with when they didn’t want to or because you made them feel like they didn’t have a choice (even though you did not use physical force or threats)?
Dating abuse [37]	Baseline - No, I have never done this to someone I was in a relationship with - Yes, I have done this in the past 9 months - Yes, I have done this, but not in the past 9 months T3: Yes/no Modeled as summary score for lifetime (baseline only) and past 9 months	X			X	*Have YOU done any of the following to someone you were going out with (like he or she was your partner/girlfriend/boyfriend, you were dating them) or hooking up with:* 1. Spread rumors about their sexual reputation, like telling people they’re ‘easy’. 2. Convinced them to have sex, after they had said no a few times. 3. Made them have sex when they didn’t want to. 4. Physically hurt them (like shoving, grabbing, slapping, punching, choking). 5. Threatened to hurt them if they didn’t do what you wanted them to do. 6. Yelled at them or destroyed something that belonged to them. 7. Called them names, like ugly or stupid. 8. Told them not to talk to others or told them who they could hang out with. 9. Showed friends or posted pictures of them naked or doing something sexual. 10. Talked about what you and your partner do sexually with your friends or peers.

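### The power statement for the primary outcome gives its control rate and detectable difference for SV, while the endpoint is any SV or ARA; no rate for that composite is given, and the stated pair of effects holds only near 20%

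*Protocol article*

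**What the plan says.** Section 2.12 ties its calculation to the primary endpoint: "For the primary outcome - any SV/ARA perpetration at Time 3, the detectable difference between arms was calculated based on traditional methods". The inputs are "assuming a within-cluster intra-class correlation (ICC) of 0.01", "a 20% baseline SV perpetration rate in the control arm", and, for numbers, "With 866 participants (approximately 41 boys at each site) and an 80% retention rate at Time 3". The result is "80% power to detect an absolute difference in SV perpetration of 8.3 (42% relative decrease) due to the intervention". ARA is named in the opening but is absent from both the assumed rate and the reported effect.

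Section 2.10.1 defines the endpoint: "The primary outcome measure for the study is any report of SV or ARA perpetration, i.e., yes to any of the following items". The items that follow in 2.10.2 to 2.10.8 are not all sexual. The dating abuse list in Table 2, for example, contains "Called them names, like ugly or stupid".

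The article also defines two component outcomes. Any ARA is a yes to any of 13 partner-directed items (2.10.1). Any SV is described at the end of 2.10.3 as the sexual relationship violence and dating abuse items together with everything listed after them.

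**The concern.** For a binary endpoint the control rate fixes the variance, so a power statement is only as good as the match between that rate and the endpoint. Here the rate carries the name of one component and the endpoint is the union of two. A union cannot be rarer than a part of it. If 20% belongs to SV alone, the composite rate is 20% or more, and any value above 20% changes both the absolute and the relative difference that the trial can detect.

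What is at stake is how the result is read. Someone who takes 8.3 points and 42% as the effect the trial could detect on its primary endpoint may draw the wrong conclusion about what a null result rules out.

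**Working it through.** **Item count.** Physical/sexual relationship violence 3, dating abuse 10, non-partner SV 2, incapacitated sex 1, alcohol or drugs 1, sexual harassment 5, cyber sexual abuse 3. The total is 3 + 10 + 2 + 1 + 1 + 5 + 3 = 25. Read literally, the any-SV definition in 2.10.3 leaves out only the physical-violence item, so it covers 24 of the 25.

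**Inputs from the article.** 866 participants, 21 clusters ("total of 21 clusters randomized, with 11 assigned to experimental and 10 assigned to control"), ICC 0.01, 80% retention, two-sided 5%, 80% power. The composite rate is not given, so the values from 25% to 60% below are assumptions.

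**Formulas.** Equal arms, normal approximation. Design effect DE = 1 + (m − 1) × 0.01. Effective size per arm n_e = n / DE. The detectable difference d solves d = (1.960 + 0.842) × √{[p(1 − p) + (p − d)(1 − p + d)] / n_e}. Power for a given d is Φ(d / SE − 1.960), where SE is the same square root without the multiplier.

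**The plan's own figure.** 8.3 / 20 = 41.5%, so the 42% agrees with the 8.3.

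- With the stated retention: 866 × 0.80 = 692.8, or 346.4 per arm; m = 692.8 / 21 = 33.0; DE = 1.32; n_e = 346.4 / 1.32 = 262.4. At p = 20%, d = 8.8 points. Power for 20% against 11.7% is 74% to 75%, depending on whether the variance is pooled.
- With no loss to follow-up: 433 per arm; m = 41.2; DE = 1.40; n_e = 308.8. At p = 20%, d = 8.2 points (8.2 to 8.3 across variance formulas and actual arm sizes), and power for 8.3 points is 81%.

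So with the stated ICC, the 8.3 is approached only when the 20% loss is left out. The standardized difference of 0.23 in the same section behaves the same way: about 0.23 without loss and about 0.245 with it. A smaller ICC with retention applied would also come close (8.25 points at 0.004, 8.45 at 0.006), but the section states 0.01 for this outcome.

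**If the composite rate is higher** (retention applied, n_e = 262.4):

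| Control rate | Detectable difference | Relative | Power for 8.3 points | Power for 42% relative |
|---|---|---|---|---|
| 20% | 8.8 | 44% | 74.6% | 76% |
| 25% | 9.7 | 39% | 65.3% | 86% |
| 30% | 10.5 | 35% | 58.8% | 93% |
| 40% | 11.5 | 29% | 51.2% | 99% |
| 50% | 12.1 | 24% | 48.2% | over 99% |
| 60% | 12.1 | 20% | 48.5% | over 99% |

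The fair baseline for the fourth column is the 74.6% in the first row, not 80%. The gap between those two comes from retention, and only the fall below 74.6% comes from the rate. Without loss to follow-up, the corresponding powers for 8.3 points are 81% at 20%, 66% at 30%, 58% at 40% and 55% at 50%.

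**The case against.** The strongest reply is that SV is shorthand. The section says outright that the calculation is for any SV/ARA. The article is loose with the abbreviation elsewhere: the heading of 2.1.1.4 speaks of SV where its text speaks of SV/ARA. The literal any-SV definition already takes in the dating abuse items, name-calling and yelling included. On that reading the two rates may be close and only a label is wrong. This stands as a possibility. It does not remove the point, because nothing in the article says which reading applies, and the citations in that sentence support the ICC, not the 20%.

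A second reply is that a higher rate helps as well as hurts. This stands in full. Power for 8.3 points falls, but power for a 42% relative decrease rises. The primary model uses a logit link, and holding the odds ratio implied by 20% against 11.7% (about 0.53) gives power of 75% at a 20% rate, 87% at 30%, 93% at 40% and 95% at 50%.

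A third reply is that recruitment is complete and a condensed article may leave the source of the 20% to the full protocol. That lowers the practical stake. It does not excuse a sentence that names one outcome and gives figures for another.

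From the everyday nature of some items, a reader might infer that the composite rate is much higher than 20% and that the trial is underpowered. The article supports neither. It reports no composite prevalence, logic yields only that the rate is not lower than that of an SV subset, and the effect on power depends on the scale.

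**Conclusion.** The mismatch is real. Section 2.12 announces the primary composite, labels both its control rate and its detectable difference as SV, and gives no composite rate. Whether 8.3 points and 42% describe the primary endpoint is therefore conditional. They do so approximately if 20% is the composite rate. If it is an SV-only rate and the composite is more common, they do not.

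Over assumed composite rates of 30% to 60%, the detectable difference is about 10.5 to 12.1 points, or 35% down to 20% relative. Power for 8.3 points is about 48% to 59%, and power for a 42% relative decrease is above 90%. Separately, at the stated 20% with the stated retention, 8.3 points has about 74% power, not 80%.

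These figures rest on ICC 0.01, equal arms, equal cluster sizes and a normal reference. A t reference with 19 degrees of freedom lowers power at the 20% rate further, to about 69% to 70%.

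**What to change.** - State which outcome the 20% refers to: SV in a narrow sense, any SV as in 2.10.3, or any SV/ARA.
- Compute the 9-month prevalence of the composite in 2.10.1 from the 866 completed baseline surveys, pooled over arms so that no treatment comparison is seen. Use it as the planning value for the control rate, noting that it stands in for the Time 3 rate.
- Restate the detectable absolute and relative differences at that rate with 80% retention applied.
- Replace SV with any SV/ARA in both places in 2.12.

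The cost is one arm-blind frequency, one recalculation and a rewritten sentence. Enrolment, endpoint and analysis stay as they are.
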